### Development of the instruments of the realistic study

The self-administered questionnaire was developed from the instruments (cited above) translated into French, and new items prepared as part of this research to characterize quality of CF care and the degree of engagement of the patients or parents. The whole questionnaire is proposed to the members of the quality teams. A limited part of the questionnaire is proposed to the members of the MDT not on the quality team. The questionnaire has been prepared from January to June 2014 with clinicians from the Nantes/Roscoff CF-CERD and experts from the Health Education and Practice Laboratory (LEPS) at the Sorbonne Paris Cité University - Paris 13 Bobigny. It has then been tested between July and September 2014 in three teams from the Nantes/Roscoff CF-CERD (pediatric, adult, and mixed) with 29 respondents from all disciplines and the patients/parents participating in the QT. As a result of these tests, the questionnaire has been slightly adapted, essentially by rewording parts of the French translation and adding free text fields (*Questionnaire available upon request to the corresponding author*).

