In 2011, the French national team at the Nantes/Roscoff CF-CERD transposed the PHARE-M quality improvement program from the US CFF QIP model (*PHARE-M: Programme Hospitalier d’Amélioration des Résultats et de l’Expertise en Mucoviscidose - Hospital Program to Improve Outcomes and Expertise in Cystic Fibrosis)*. It was launched in September 2011 with a pilot phase (2011–2012) involving seven volunteer CFCs, which underwent two external assessments, leading to certain adjustments to the initial program. This adjusted version was deployed during a regional expansion phase (2012–2013), including seven more CFCs before its national deployment [10]. The main adjustments consisted in more practical exercises during face-to-face meetings (less theoretical presentations), more on-site coaching to help the quality teams analyze their processes of care, and the designation of a PHARE-M referent in each local team to keep focused on the QI work. These 2 years are called the “experimental phase”, which involved 14 CFCs.

The two evaluations at the end of the one-year pilot phase showed the progressive adherence of the teams and improvements in care management, but a limited impact on patient health outcomes. They also highlighted that the adherence to the program mainly depended on the motivation of the multidisciplinary team (MDT), especially its lead physician. The lack of resources at some CFCs was raised to account for variations in the teams’ engagement as the level of available staff seemed to influence the extent to which the team was effectively enlisted. The participation of a patient or parent in each local quality team varied depending on the cultural context of the centers, some being used to share information with patients/parents, having a patient group in the CF center for years, others being involved in patient therapeutic education while others were acting in a more partenalistic model of care. The support received from the hospital quality department in two hospitals was emphasized as a factor that facilitated the adoption of quality tools by the teams. The recommendation of the assessor was to evaluate the impact of the program on patient outcomes by 2015.

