**Fig. 3 Fig3:**
[figure not shown]
Modeling of the intervention, context, and mechanisms

The PHARE-M intervention consisted of establishing, training and coaching a quality team (QT) at each CFC comprising a number of professionals from the multidisciplinary CF team and 1 parent or patient from the CFC’s caseload. The members of the QT have been trained in quality methods and tools and coached in changing care processes. The PHARE-M intervention should have directly impacted the ability of the local QT to master QI methods and tools, lead changes in the care processes, and should have generated good appreciation of the utility of the QT efforts. This direct impact of PHARE-M is identified under the heading “QT effectiveness”. QT effectiveness may not only be the result of the PHARE-M intervention but may have been modulated by internal mechanisms, such as the composition of the QT (number of members and disciplines enlisted), its functioning (rigor in the QI work, decision-making, clarity of the roles…) and the parent or patient engagement. Those mechanisms are represented as impacting QT effectiveness (Table 3). Beyond the ability to master the QI methods and tools, the PHARE-M intervention was expected to have an impact on the quality of CF care delivered at the CFC. The Chronic Care Model [12] was deemed appropriate to account for quality of CF care across the 6 dimensions: existing improvement goals, multidisciplinary care, self-management support, decision support (use of evidence-based guidelines), use of information system and electronic patient record, and organization of resources in the patient’s community of life. Finally, an indirect impact of the PHARE-M intervention is expected on the trend in patient outcomes’ evolution as measured in the quantitative part of this study. Moreover, some elements in the CFC contexts, which are external to the PHARE-M intervention and preexisted to its introduction, may have had a major impact both on the adherence of the team to the QI work and on its outputs. The contextual elements that have been brought in this study include the composition of the MDT, the leadership, the patient-centeredness of care, the innovative culture of the team, and the support from the hospital quality department.

The qualitative study will test these hypotheses using a questionnaire to be self-administered, in 2015, to all members of the MDT at the 14 CFCs and to the patients/parents participating in the quality teams.

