Quality of care has been defined according to the criteria of the Chronic Care Model [12]; as this model has not been popularized in France nor in cystic fibrosis, we adapted it with 47 items aimed at characterizing CF care. Table 4 presents a list of these items.

**Table 4 Tab4:** Criteria for quality of CF care derived from the chronic care model

IG — Improvement Goals at the CFC	1 — There are improvement goals at the CFC
	2 — These goals, if they exist, are the subject of both indicators and an action plan at the CFC
	3 — The CFC has tools to follow up this action plan in the form of a dashboard
	4 — To your knowledge, this action plan has been discussed with management and validated
SMS — Self-Management Support - Therapeutic Patient Education	1 — To your knowledge, there is a therapeutic education program for patients at the CFC authorized by the French regional health agency (ARS)
	2 — In your opinion, the professionals at the CFC are well trained in TPE
	3 — More than 80% of the patients/parents attended at least one TPE session in the last year
	4 — The total time spent by the professionals on TPE is sufficient
	5 — There are no obstacles to implementing TPE at the CFC
	6 — The team is involved in the studies of one of the French national groups on therapeutic education via face-to-face participation or regular reporting of information
	7 — The CFC has priority objectives for developing TPE
	8 — If yes, the CFC has indicators to follow up the achievement of these priority objectives
MM — Multidisciplinary management	1 — To your knowledge, the multidisciplinary team at the CFC comprises all the disciplines recommended by the French National Diagnosis and Treatment Protocol (PNDS): specialist physician, nurse, physiotherapist, psychologist, secretary, and social worker
	2 — The number of staff in all disciplines is sufficient for the number of patients followed up
	3 — In your view, the multidisciplinary team seems stable over time (the professionals’ turnover rate is below 20% in a year)
	4 — The members of the multidisciplinary team have a great deal of expertise in managing cystic fibrosis
	5 — The multidisciplinary team meets often enough to perform a summary of the records of the patients who have come to the CFC
	6 — During these multidisciplinary meetings, the team generally reviews the records of the patients with a scheduled visit to the CFC

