	2 — The team has an electronic patient record system that allows it to view changes in the patient health outcomes (nutritional and respiratory outcomes) over the course of several years
	3 — The team uses the electronic patient record system during the multidisciplinary staff meetings
	4 — The team displays information from the electronic patient record during the multidisciplinary meeting (graphs of changes over time, reports from previous consultations with different professionals, etc.)
	5 — The team uses the electronic patient record system both to create alerts on applying recommendations for the patient and to compile statistics on the population followed up
	6 — The team uses the electronic patient record system to include biology results
	7 — The team uses the electronic patient record system to include imaging results
	8 — The electronic patient record system helps in selecting patients for clinical trials
	9 — The electronic patient record data are automatically transmitted with a good degree of reliability (minimal verifications, corrections, and additions) to the French Cystic Fibrosis Registry
SN — Staff in the networks in the community	1 — The CFC has organized a network of professionals in the patient community for managing care at home
	2 — The CFC organizes regular trainings for professionals in the patient community
	3 — The CFC regularly evaluates the professionals caring for CF patients in the community
	4 — The CFC assesses the health providers of devices managing CF patients
	5 — The CFC assesses the needs for home care and its distribution between professionals and carers for a balanced organization of home care
	6 — The CFC provides the patients with offers of sports activities, creative activities, and psychological support near their place of residence

QT effectiveness has been described in the studies by Lemieux-Charles [17] and Shortell [18]: it is characterized according to 27 items (see Table 5).

**Table 5 Tab5:** Effectiveness of a quality team (QT)

Command of the quality process and tools	1. The teams that implement a quality process have a clear vision of the area on which to focus their improvement efforts and the expectations to be met. When you started the project, did you have such a vision?
	2. The quality teams sometimes use a method for making progress, such as a guide to follow step by step which helps them organize their work. Did your team use such a structured method?

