Effectiveness perceived by the rest of the team	1. I believe that the work of the steering team was useful for improving quality at the CFC.
	2. I believe that the entire team at the CFC was enlisted and contributed to quality improvement.
	3. I believe that the outcomes achieved collectively meet the organization’s needs for improvement.
	4. I believe that it is necessary to maintain an ongoing quality improvement process to continuously improve management at the CFC.

QT Internal factors that may have modulated the QT effectiveness: QT functioning [17] is characterized by 22 items classified in 4 categories 1) the organization at work, 2) the decision-making process, 3) the shared improvement goals, and 4) the ability to communicate and get external support. Studies by L. Lemieux-Charles defined these items to analyze the impact of adopting quality improvement practices on the internal functioning of a team. We use the same items to analyze if the team’s functioning could modulate its effectiveness (see Table 6).

**Table 6 Tab6:** Internal functioning of the quality team (QT)

Strictness of organization and clarity of roles	1. The leader was clear and explicit on how he or she wanted the team to work.
	2. The leader reviewed the steering team’s work and asked how we were going to go about it.
	3. The leader also requested the opinion of the other members of the team.
	4. The leader’s behavior reflected the importance he or she placed on the quality team functioning well.
	5. Our team could have been better at seeking help and securing more skills to do the work.
	6. Sometimes it seemed that we were working or going about the matter in the wrong way.
	7. Roles were so unclear that the work of different individuals seemed to overlap.
	8. The members of the team had different outlooks and experiences and came from different disciplines.
Decision- making on the QT	1. Most of the members of the team had an opportunity to participate in decision-making.
	2. We appreciated our differences, which shaped our decisions.
	3. The contribution of each member of the team was heard and taken into consideration.
	4. We examined many different ideas before making a decision.
	5. Our team possessed sufficient resources and skills and applied them well enough to work properly.
	6. Our team worked well enough to accomplish its mission satisfactorily.
Clarity of objectives	1. The members of the team were in agreement on the objectives of the project.

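### Backward-looking quality-team items have no membership-period rule, and 'Unknown' scores 0, so members without first-hand knowledge can lower a center's effectiveness score

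*Protocol article*

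**What the plan says.** All references are to the protocol article.

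- **Timing of the intervention.** The Background describes a pilot in 2011–2012 with seven centers and an expansion in 2012–2013 with seven more: "These 2 years are called the “experimental phase”, which involved 14 CFCs".
- **Timing of the survey.** Under Qualitative study, Design: "The qualitative study will test these hypotheses using a questionnaire to be self-administered, in 2015, to all members of the MDT at the 14 CFCs". Patients and parents on the quality teams are also surveyed. No earlier round of this questionnaire is described.
- **Respondents.** Under Development of the instruments of the realistic study: "The whole questionnaire is proposed to the members of the quality teams". For the others: "A limited part of the questionnaire is proposed to the members of the MDT not on the quality team". Neither sentence sets a date or length of membership.
- **Items.** Table 5 asks, for example, "When you started the project, did you have such a vision". Table 6 is mostly in the past tense, for example "The leader was clear and explicit on how he or she wanted the team to work". Some items are in the present tense, and none names calendar years.
- **Scoring.** Under Analyses of responses and validation of the questionnaire, items run from 1 (*Completely disagree*) to 4 (*Completely agree*). *No* and *Unknown* both receive 0. Scores are rescaled to 100 and totalled by theme.
- **Use.** The same section relates quality-team effectiveness to quality of care. It then crosses the survey results with the 2011–2015 changes in patient indicators to look for a signature of factors that go with high or low impact.

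**The concern.** Only someone who was on the team can say whether it had a clear vision at the outset or how its leader wanted it to work. The survey comes about two to four years after training, so some members may have joined since. Such a person can answer *Unknown*, which the scoring rule counts as worse than complete disagreement, or can guess.

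The first response lowers the score for a reason unrelated to what the team did. The second adds error whose direction cannot be predicted.

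Quality-team effectiveness and functioning are meant to help explain differences between the 14 trained centers. If a low score can mean either that the team worked poorly or that its members are new, an association with that score cannot be read as the mechanism the article proposes. Team stability is also one of the quality-of-care items (Table 4, multidisciplinary management, item 3). Turnover could therefore lower the explanatory score and, through that one item, the score it is meant to explain.

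**Working it through.** The article reports no figure on this point to reproduce. The check follows the scoring rule as written.

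**Inputs from the article**
- Item range 1 to 4; *Unknown* = 0; rescaling to 100.
- About 130 respondents over 14 teams, so 130/14 = 9.3 per center. This includes multidisciplinary-team members outside the quality team.

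**Assumptions**
- Theme score = 100 × mean item score / 4. The article says only that the score is reset to 100.
- Informed members average m.
- A share f of respondents answers *Unknown* on every item of the theme. The article does not give f.

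**Step 1. Effect of the zero.**
Score = 100 × [(1 − f)·m + f·0]/4 = (1 − f) × 25m.

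The relative loss is f under any proportional rescaling, so it does not depend on the divisor of 4.

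| f | m = 2.5 | m = 3 | m = 3.5 |
|---|---|---|---|
| 0 | 62.5 | 75.0 | 87.5 |
| 10% | 56.2 | 67.5 | 78.8 |
| 20% | 50.0 | 60.0 | 70.0 |
| 30% | 43.8 | 52.5 | 61.2 |
| 50% | 31.2 | 37.5 | 43.8 |

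With *Unknown* treated as missing, each column stays at its first-row value whatever f is.

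**Step 2. Not knowing against disagreeing.**
If the same share answered *Completely disagree* (1), with m = 3, the score would be 100 × [3(1 − f) + f]/4 = 75 − 50f. At f = 20% this is 65, against 60 for *Unknown*. Not knowing costs 25f points more than full disagreement, here 5 points.

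**Step 3. What a full Likert step takes.**
One step is 25 points. From 75, 75f = 25 gives f = 1/3. Of 9.3 respondents that is about 3 people, and fewer where the quality team is smaller than the whole respondent group.

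**Step 4. Could f be that large?**
The article reports no quality-team turnover. If turnover were a constant rate t per year with every leaver replaced (assumption), the share who joined since is 1 − (1 − t)^y:

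| t | 2 years | 3 years | 4 years |
|---|---|---|---|
| 10% | 19% | 27% | 34% |
| 20% | 36% | 49% | 59% |

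These shares are ceilings for f. They equal f only if every late joiner answers *Unknown* throughout. If late joiners do so on only a fraction g of the items, f in step 1 is replaced by f·g.

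**The case against.** The strongest reply is that the article does not say the respondents are whoever sits on the team in 2015. The Design section describes quality-team members as people who were trained and coached, so the questionnaire may be meant for those members. This stands in part. Supervised completion during a site visit in 2015 makes current members the natural reading, but it remains an inference. So does any claim that departed members are left out.

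A reader might also infer that the items ask strictly about 2011–2013. They name no period and some are in the present tense. A later joiner may have seen tests of change at first hand.

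A reader might further infer that turnover is always scored as poor effectiveness, or that about half the respondents in a stable center were absent from training. The documents do not support either. The penalty operates only through the zero for *Unknown* (or *No*). The 20% figure is the limit in one questionnaire statement, "turnover rate is below 20% in a year". It concerns the whole multidisciplinary team and is not a measurement.

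Two safeguards exist. Focus groups at all 14 centers are to be compared with pilot-phase interviews at the first seven, which covered functioning. Center results are returned to each team to validate their interpretation. Neither corrects the scores: the interviews cover half the centers and are compared with the focus groups, and no rescoring follows the feedback.

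Finally, the full questionnaire is not shown, so an item on date of joining may exist. Even so, the scoring rule is stated without exception, and tenure is not among the stated groupings of responses.

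**Conclusion.** The point holds as a gap in the respondent definition combined with a scoring rule that has a known direction. As written, a quality-team member without first-hand knowledge who answers *Unknown* lowers the center's score in proportion to the share of such answers. From 75 the score falls to 60 at 20% and to 50 at one third. These figures assume proportional rescaling with division by 4, informed members averaging *Agree*, and *Unknown* on all items of the theme. The actual share of *Unknown* answers and the actual quality-team turnover are not in the document, so the size at any center cannot be stated.

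Turnover can pass for low effectiveness; the article does not show that it does. The analysis concerned is descriptive, and the FEV1 and BMI comparison is untouched. This is a cheap improvement to the explanatory part of the study.

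**What to change.** 1. Add one item on when the respondent joined the quality team, in broad categories (for example, before or during the center's training year, or later). Exact dates could identify people, because teams are small and responses are processed anonymously.
2. On the retrospective items of Tables 5 and 6, treat *Unknown* as missing instead of 0, keep it separate from *No* in the data, and report its share per center.
3. Report per center how many respondents were members during the training period.
4. Present the retrospective theme scores stratified by membership period, or add a sensitivity analysis restricted to members present in their center's training year. With about nine respondents per center, including people outside the quality team, a hard filter for the main score would leave too few.

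If answers have already been collected, step 2 needs only rescoring, provided *No* and *Unknown* were stored separately.

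The cost is one extra item and a change in scoring. The downside is fewer answers behind each retrospective score, so center scores become noisier.

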### On-site investigations

The investigations conducted by the clinical research assistant at the 14 PHARE-M centers take place over the course of 2.5 consecutive days per CFC. The questionnaire is self-administered successively under the supervision of the clinical research associate according to a schedule established with the team at the site, with no possibility of communication or consultation among respondents. The questionnaires and responses are managed in SurveyMonkey Software and subsequently exploited using SAS and Excel Software. The focus group is conducted at the end of the visit. Each focus group is recorded using audio equipment and transcribed in writing.

### Analyses of responses and validation of the questionnaire

Responses to the items of the questionnaire are processed anonymously. Each item receives a score on a Likert scale from one to four based on the degree to which the respondent agrees or disagrees with the proposition: “Completely disagree; Disagree; Agree; Completely agree”. “No” and “Unknown” responses are assigned a score of 0. The score is reset to 100 points and can thus be totaled by theme of the questionnaire and category of respondents. An initial descriptive analysis of the responses by CFC is returned to each quality team in the month following the on-site investigation, via a web conference, in order to validate the interpretation of the scores for the different themes and identify avenues for or obstacles to continuous care quality improvement at the CFC.

A Cronbach’s alpha test will be performed on all responses collected at the centers. Since the anticipated number of respondents is around 130 people in total for the 14 teams, this test will not allow the questionnaire to be modified for use in a larger population of respondents. It mainly aims to validate the French translations of the parts of the questionnaire coming from previous studies in English and discuss the use of the parts created within this research study.

A second level of descriptive analysis will be performed by aggregating the responses (all CFCs, by professional discipline, for resource patients/parents, and for professionals) to search for potential associations between quality of care at the CFC 3 years after the PHARE-M intervention and the effectiveness of the QT and/or the engagement of parents/patients and/or contextual elements.

After the publication of the Registry report presenting the 2015 data, changes in indicators from 2011 to 2015 will be crossed with the results of the realistic part of the study, in an attempt to identify any association in relation with more favorable changes over time in patient outcomes. A “signature” set of factors associated with a maximum/minimum impact of the PHARE-M will be sought.

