	2. The achievement of the objectives guided the activities of the members of the team.
	3. The members of the team did what was expected of them.
	4. The members of the team were all focused on the achievement of the same objectives.
Communication and cooperation	1. There was a great deal of cooperation between the different hospital departments.
	2. In this hospital, most departments and services have a hard time sitting down at a table and solving problems together.
	3. The people I worked with were comfortable with suggesting changes and improvements.
	4. Our team received all the information required to plan and organize its work.

The engagement of the patient/parent as characterized in Carman’s framework [19] is assessed by a list of 31 items, prepared as part of this research (see Table 7).

**Table 7 Tab7:** Engagement of the patients/parents on the quality team (QT)

Information and activation of the patients/parents	1. The patients and parents are educated regularly (annually or more often) by the team about general subjects concerning cystic fibrosis care and research.
	2. The patients and parents are rather familiar with general cystic fibrosis information: research, progress made, and Registry data.
	3. The CFC team has educated the patients and parents about the PHARE-M’s importance and aim.
	4. A good relationship between the patient or parent recruited and the team is indispensable for the patient or parent to participate in the PHARE-M.
	5. The patient or parent recruited is well informed of the challenges (10 commitments) of management quality.
	6. The presence of a patient or parent on the steering team is a given and an asset.
	7. The place of a parent or patient is not on a quality team, because he or she does not have enough training or education.
	8. The place of a parent or patient is not on a quality team, because he or she already has too many personal problems to manage.
	9. The patient or parent recruited possesses the qualities to become a member of the steering team.
	10. The patient or parent recruited must have developed coping skills (see therapeutic education standard: knowing how to manage emotions and stress; solving problems, making decisions, and making choices; knowing how to communicate and being adept in relationships with others; and knowing how to put oneself in the place of others).

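### The questionnaire rule scores 'Unknown' as 0, below the strongest disagreement, and makes no provision for reversing adversely worded items

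*Protocol article*

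**What the plan says.** The rule is in the protocol article, under 'Analyses of responses and validation of the questionnaire'. It reads: "Each item receives a score on a Likert scale from one to four based on the degree to which the respondent agrees or disagrees". The categories are listed as "Completely disagree; Disagree; Agree; Completely agree". The list order implies 1 for the first category and 4 for the last. 'No' and 'Unknown' "responses are assigned a score of 0". Then: "The score is reset to 100 points and can thus be totaled by theme of the questionnaire and category of respondents".

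The scores have four stated uses in the same section: a descriptive report returned to each centre, Cronbach's alpha on all responses (mainly to validate the French translations), a search for associations of quality of care with quality-team effectiveness, engagement and context, and a crossing with the 2011 to 2015 changes in patient indicators to look for a 'signature' of factors.

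Six of the items shown are worded so that agreement is unfavourable:
- Table 6, strictness of organization, items 5 and 6: the team could have sought help better, and at times went about the work wrongly.
- Table 6, strictness, item 7: "Roles were so unclear that the work of different individuals seemed to overlap".
- Table 6, communication, item 2: "In this hospital, most departments and services have a hard time sitting down at a table and solving problems together".
- Table 7, items 7 and 8, which both open with "The place of a parent or patient is not on a quality team".

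The article neither provides for reverse-scoring nor rules it out.

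**The concern.** An 'Unknown' answer says something about the respondent. Scoring it 0 turns it into the worst possible statement about the centre, one point below complete disagreement. Several Table 4 items ask for facts that a given nurse, psychologist or parent may not have: whether an action plan was validated with management, whether more than 80% of patients or parents attended an education session, whether record data pass reliably to the Registry. Theme scores then mix quality of care with familiarity with the centre.

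This bears on the study's own question. If the same people answer 'Unknown' on quality-of-care items and on team-effectiveness items, the zeros lower both scores together and can create or inflate an association between them.

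'No' = 0 raises a related question. It may be meant only for yes/no questions, such as the first block of Table 5, but the text does not limit it to them.

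If the agreement score is also applied unreversed to the six adverse items, agreeing with a criticism raises the score. Alpha would then suffer for a reason unrelated to the translation it is meant to check.

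**Working it through.** The article gives no reliability figure or expected 'Unknown' rate, so there is nothing to reproduce. The check applies the written rule.

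**Inputs.** Scores 1 to 4 and the 0 for 'Unknown' come from the scoring section; item counts come from Tables 4, 6 and 7. Assumption: theme score = 100 × sum of item scores / (4 × number of items). The article says only that the score is reset to 100 points.

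**Effect of 'Unknown' = 0**
- Information system (9 items), six 'Agree' and three 'Unknown': 6 × 3 + 3 × 0 = 18, and 18/36 = 50. On the six answered items: 18/24 = 75. Had the three been 'Completely disagree': 21/36 = 58.3.
- Improvement goals (4 items), three 'Agree' and one 'Unknown': 9/16 = 56.25. On answered items: 9/12 = 75. With 'Completely disagree' as the fourth answer: 10/16 = 62.5.
- A respondent who knows nothing about a theme scores 0; one who completely disagrees throughout scores 25.
- About 130 respondents in 14 teams is 130/14 ≈ 9 per centre. If eight score 75 and one answers 'Unknown' throughout the theme, the centre mean is 600/9 ≈ 67.

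**Effect of no reversal, if the rule is applied literally**

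| Theme | Items (adverse) | Best possible | Worst possible |
|---|---|---|---|
| Strictness | 8 (3) | (5×4 + 3×1)/32 = 71.9 | (5×1 + 3×4)/32 = 53.1 |
| Communication | 4 (1) | (3×4 + 1)/16 = 81.25 | (3×1 + 4)/16 = 43.75 |
| All of Table 6 | 22 (4) | (18×4 + 4×1)/88 = 86.4 | (18×1 + 4×4)/88 = 38.6 |
| Table 7, items shown | 10 (2) | (8×4 + 2×1)/40 = 85 | (8×1 + 2×4)/40 = 40 |

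With reversal, and only categories 1 to 4 used, each range is 25 to 100. Without it, a respondent who ticks 'Completely agree' throughout scores 100 on strictness, above the 71.9 of a perfectly functioning team.

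**Effect on alpha (illustrative simulation).** Assumptions: 130 respondents, one factor, 4-point items, latent inter-item correlation 0.3 to 0.5, and 'Unknown' answers falling at random.
- Eight correctly keyed items without zeros: alpha 0.73 (correlation 0.3) to 0.86 (correlation 0.5).
- The same items with 5% 'Unknown' scored 0: 0.60 and 0.75. With 20%: 0.37 and 0.51.
- No reversal, no zeros: strictness falls to about −0.2 to −0.3; communication from 0.58–0.75 to about 0; all of Table 6 from 0.88–0.94 to 0.70–0.81; the ten Table 7 items from 0.77–0.89 to 0.45–0.58.

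Random 'Unknown' answers lower alpha. If they cluster within respondents instead, the shared zeros add covariance between items and could raise it. Either way, alpha no longer measures only the consistency of the answers.

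**The case against.** The strongest objection concerns reversal. A reader might infer that the adverse items are, or certainly will be, scored as if agreement were favourable. The documents do not support that. The article is silent on item direction, the Table 6 items come from a cited instrument, the questionnaire is available on request, and item coding is a detail that a condensed article may leave to the full protocol. What stands is narrower: the rule, worded for each item, makes no exception, so the keying needs to be confirmed.

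The reach is also limited. The adverse items fall in two of the four Table 6 themes and in Table 7, where only 10 of 31 items are shown. Tables 4, 5 and 9 are worded positively or neutrally, and Table 8 uses its own allocation of 100 points. Mis-keyed items would probably show up as negative item-total correlations when alpha is run.

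A reader might also infer that centre scores move with respondent mix alone. The plan totals by respondent category, and team members outside the quality team receive only part of the questionnaire. That handles mix in part, but not differences in knowledge within a category.

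Finally, a low score for 'Unknown' has some logic for certain items, since a dashboard that staff have never heard of is arguably not working. Treating it as missing has its own bias, because those who can answer may be the most involved. This supports keeping the 0 coding as a sensitivity analysis. It does not justify it as the only rule, least of all for opinion items.

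**Conclusion.** The 'Unknown' half holds on the text: the rule is printed, and it ranks lack of knowledge below the strongest disagreement. The distortion in an individual theme score can be large (50 against 75 in the information-system example). Its size in the study depends on the 'Unknown' rate, which the article does not give, and on the assumed divisor. The documents therefore show that results will be distorted to the extent that 'Unknown' answers occur; they do not show that every score or association will be wrong.

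The reversal half is conditional. The ceilings of 71.9 and 81.3 apply only if the rule is followed literally. The alpha figures rest on the simulation assumptions and are illustrative.

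This is a moderate issue. The FEV1 and BMI slope comparison does not use these scores, and the questionnaire analyses are described as descriptive. The scores do feed the centre feedback, the validation of the instruments and the crossing with patient outcomes, and the article foresees further use of the questionnaire, which would carry the rule forward.

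**What to change.** - Treat 'Unknown' as missing. Score each theme as the mean of the answered items, rescaled to 100, with a stated minimum number answered.
- Report the 'Unknown' rate by centre and respondent category, and keep the 0 coding as a sensitivity analysis.
- State which items take 'No' = 0. If 'No' can be given on a four-point item, explain how it differs from disagreement.
- Confirm that Table 6 strictness items 5, 6 and 7, communication item 2, and Table 7 items 7 and 8 are reverse-scored (5 minus the score), or apply it. Check the Table 7 items not shown for the same wording.
- Compute alpha, the associations and the crossing with patient outcomes only after these steps.

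The cost is small. Responses are managed in SurveyMonkey and processed in SAS and Excel, so this is recoding, with no new data collection. The downside is that feedback goes to each centre within a month of the visit, so scores already returned may have to be re-issued.
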